## Abstract

**Background:**

Neck pain caused by cervical spondylosis (CS) has become one of the most common health problems around the world. Electroacupuncture (EA) has been employed to relieve CS neck pain, but there is limited clinical evidence for its effectiveness.

**Methods/Design:**

This study consists of a randomized controlled trial (RCT) with two parallel arms: an acupuncture group and an EA group. Both groups will receive acupuncture at *Jing-jiaji* points for 30 minutes each time, for five sessions per week for a total of 20 sessions during this four-week period. In addition, the EA group will be connected with EA apparatus. The following outcome measurements will be used in examination of subjects: the Northwick Park Neck Pain Questionnaire (NPQ), McGill Pain Questionnaire (MPQ), and Short-Form 36 (SF-36) scale. All these outcomes will be examined at the start of the study, at the end of the second week, at four weeks after randomization, and one and three months after treatment cessation respectively.

**Discussion:**

This study aims to assess the efficacy of EA, compared with acupuncture intervention at *Jing-jiaji* points for the CS neck pain.

**Trial registration:**

Chinese Clinical Trials Register:
ChiCTR-TRC-13003422.

## Background

Cervical spondylosis (CS) is defined as an age-related chronic disc degeneration, which is caused by unspecified degenerative changes of the muscles, tendons, joints, and bones of the neck and shoulder
[1]. Its etiology involves several factors, such as poor posture, anxiety, depression, neck strain, and sporting or occupational activities
[2]. The main symptoms of CS are neck pain and stiffness, even radiating to the shoulders, and sometimes accompanied by numbness and radicular pain in the arms and fingers.

The prevalence and incidence of neck pain caused by CS have been reported in several studies. For example, the overall prevalence of neck pain rates vary from 0.4% to 86.8% (mean 23.1%) and the incidence of neck pain rates fluctuate from 10.4% to 21.3% in a high-risk population (office and computer workers)
[3]. In the UK, about two-thirds of adults suffer from the experience of neck pain at some time in their lives
[4]. A household survey was conducted in Hong Kong showed that the prevalence of CS neck pain to be 15% to 17%, and the lifetime prevalence to be 30% to 50%
[5].

Conventional medical treatments for CS neck are limited by their modest effectiveness
[6]. These kinds of treatments include administration of NSAID drugs
[7], muscle relaxants
[8], physiotherapy
[9], analgesics
[10], stress management
[11], and so on
[12].

Traditional Chinese medicine interventions, such as Chinese herbal medicine
[13], acupuncture
[14], massage
[15], cupping therapy
[16], and neck exercises
[17] have been widely used for the management of CS neck pain. Of those, acupuncture is one of the most popular measures.

In China, the evidence-based potentiality for effective use of acupuncture in the treatment of CS neck pain has been suggested
[1,14,18-22]. However, the current level of evidence is poor due to the scarce good quality studies, small sample size, short duration, rare follow-up, and variation in the composition of acupuncture. In addition, two rigorously designed RCT protocols of acupuncture for CS neck pain have recently been published
[23,24]. However, the efficacy of EA for CS neck pain has not been reported specifically. Considering these methodological flaws, we will conduct a trial to assess the efficacy of EA at *Jing-jiaji* points (extra point; six points in three pairs, bilateral, 12.5 mm horizontally away from the corresponding cervical vertebra) for CS neck pain and the feasibility of a large clinical trial.

## Methods/Design

### Objective

The primary objective of this study is to evaluate the efficacy of EA intervention for CS neck pain.

### Design

A randomized, assessor- and analyst-blinded, controlled trial to compare EA an group with an acupuncture group (Figure 
1, Table 
1) will be consisted in this study. This trial will be conducted at the Second Affiliated Hospital of Heilongjiang University of Traditional Chinese Medicine.

**Figure 1 F1:**
[figure not shown]
Flow chart of study process.

**Table 1 T1:** Timing of visits and data collection

	**Week - 1**	**Week 0**	**Week 2**	**Week 4**	**1 month**	**3 months**
	**Baseline**	**Treatment phase**			**Follow-up phase (end-of-treatment)**	
Patients						
Informed consent	**×**					
Sign the informed consent		**×**				
Medical history	**×**					
Physical examination	**×**					
Randomization		**×**				
Intervention						
Electroacupuncture group (n = 18)		20 sessions of EA at *Jing-jiaji* points				
Comparisons						
Acupuncture group (n = 18)		20 sessions of acupuncture at *Jing-jiaji* points				
Outcomes^a^						
NPQ		**×**	**×**	**×**	**×**	**×**
MPQ		**×**	**×**	**×**	**×**	**×**
SF-36		**×**	**×**	**×**	**×**	**×**
Participants safety						
Adverse events		**×**	**×**	**×**	**×**	**×**

^**a**^NPQ, Northwick Park Neck Pain Questionnaire; MPQ, McGill Pain Questionnaire; SF-36, Short-Form 36 Scale.

This trial will include a four-week treatment period and a three-month follow-up period. After randomization, patients will receive 20-session treatments over a period of four weeks. Outcome measurements will be assessed at baseline (that is, one week after subjects are diagnosed with CS), as well as at the end of the second week and four weeks after randomization, and one and three months after conclusion of the treatment phase respectively. Patients will be informed that they may be assigned to an EA group, or an acupuncture group.

This trial will be carried out according to the principles of the Declaration of Helsinki (version Seoul 2008). This study protocol has been approved by the ethics review boards of the Second Affiliated Hospital of Heilongjiang University of Traditional Chinese Medicine, with permission number LLP2012029. All participants will be asked to provide written informed consent before enrollment having been given adequate time to consider what the trial involves. For subjects who decline to agree to participate in EA, other treatment options will be available.

### Randomization and allocation concealment

A randomization scheme will be conducted by the Evidence-Based Medicine Center of the Second Affiliated Hospital of Heilongjiang University of Traditional Chinese Medicine. According to a random sequence table, generated by SAS 8.2 software (SAS software (Beijing) Co., Ltd, [name]), participants who meet the inclusion criteria will be allocated randomly into an EA group and an acupuncture group in a 1:1 ratio. Two separate databases will be set up. One (participants’ database) includes basic information on issues such as name, contact details and so on, while the other (randomization database) holds data on patients registered in the trial and their allocation
[25]. The randomization sequence schedule of group assignments and detailed treatments will be prepared by the Evidence-Based Medicine Center of the Second Affiliated Hospital of Heilongjiang University of Traditional Chinese Medicine and sealed in opaque envelopes. These sealed envelopes will be marked with the patients’ sequential numbers and kept by the screeners, who are not involved in the study.

### Blinding

The acupuncturists are in charge of sending randomization information and also receiving notices of the group assignation. As we know, it is not practical to blind the acupuncturists to treatment allocations and patients’ symptoms. In addition, it is not possible to prevent subjects from knowing whether they have received EA treatment or acupuncture intervention. However, it is feasible to blind outcome assessors and statisticians.

### Recruitment

Participants will be recruited via advertisements and posted notices. A data compilation form including the variables of interest will be completed by the corresponding researchers at each center. The obtained information will be recorded on an electronic database at each center, for subsequent statistical analysis.

## Eligibility

### Inclusion criteria

Participants will be included if they fulfilled the following criteria: (1) they are 18 to 75 years old (both male and female patients are included); (2) have a confirmed diagnosis of CS neck pain in accordance with the diagnostic criteria published by the Chinese Association of Rehabilitation Medicine (2010)
[26] and with reference to the International Classification of Diseases, 10th edition (ICD-10) codes (
http://www.icd10data.com): M47.812 (other spondylosis without myelopathy or radiculopathy (cervical region))
[27]; (3) have a diagnosis of CS supported by a cervical radiographic examination, such as anteroposterior and lateral X-rays, or magnetic resonance imaging/computed tomography scans showing cervical spine degeneration or cervical disc herniation; (4) their main symptom is of neck pain with pain intensity of more than three points as measured on a visual analog scale (VAS) upon recruitment; (5) no acupuncture therapy or other relative treatment has been received within the last seven days prior to study entry; and (6) an informed consent document has been signed.

### Exclusion criteria

Patients with any of the following conditions will be excluded: (1) history of neck trauma, cervical fracture or cervical surgery, congenital spinal abnormality, or a diagnosis of systemic disease of the bones or joints of neck; (2) vertebral body or spinal canal cancer, tuberculosis, or severe osteoporosis; (3) complications of severe systematic diseases such as cardiocerebrovascular disease, tumors, diabetes mellitus, kidney disease, or digestive system disease; (4) pregnancy or lactation; (5) rejection or fear of acupuncture therapy; (6) use of any type of acupuncture within the seven days prior to study entry; and (7) use of any other treatments (drug or non-drug).

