### Treatment group

In addition to normal acupuncture treatment, EA apparatus (Bio Medical™ Life Systems (
http://www.bmls.com; [contact])) will be connected to the needles for 30 minutes with interrupted waves (0.5Hz, 1 mA), five sessions a week for four weeks.

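### Eligibility does not confirm, before allocation, that a patient is suitable for electrical stimulation, the only thing that differs between the arms

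*Protocol article*

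**What the plan says.** **What differs between arms.** Under Intervention, both groups share points, needles and insertion depth. The Acupuncture group and Treatment group sections give the same session length and schedule. The EA arm adds apparatus that "will be connected to the needles for 30 minutes with interrupted waves (0.5Hz, 1 mA").

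**Who is kept out.** Exclusion criteria: "5) rejection or fear of acupuncture therapy" is the only criterion about accepting the trial treatment. Inclusion 5 and exclusions 6 and 7 concern earlier or other treatment. Exclusion 3 covers "complications of severe systematic diseases such as cardiocerebrovascular disease, tumors, diabetes mellitus, kidney disease, or digestive system disease". No inclusion or exclusion criterion mentions electrical stimulation.

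**Consent.** Inclusion criteria: "6) an informed consent document has been signed". The Design section adds "Patients will be informed that they may be assigned to an EA group, or an acupuncture group" and "All participants will be asked to provide written informed consent before enrollment". Shortly after that comes "For subjects who decline to agree to participate in EA, other treatment options will be available". Table 1 places the signing of consent and randomization in the same Week 0 column.

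**Blinding.** "it is not possible to prevent subjects from knowing whether they have received EA treatment or acupuncture intervention".

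**Analysis set.** The Analysis section restricts its ITT population to randomised patients who had one session or more.

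**The concern.** In a two-arm randomised trial, every patient should be able to take either treatment at the moment of allocation. Here the criterion about accepting treatment names the component that both arms share and leaves out the one that separates them. A patient who can be needled but is not suitable for current can meet every listed criterion, sign consent in good faith and be randomised. If allocated to acupuncture, that patient simply continues. If allocated to EA, the problem surfaces only then, if at all.

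Three things are at stake:
- **Selection.** Loss for this reason falls on one arm and depends on allocation. The EA group becomes slightly selected; the acupuncture group does not.
- **Safety.** Suitability is not checked before the patient is committed to an arm.
- **Feasibility.** The trial is a pilot meant to inform a larger one. Losses caused by the entry criteria would be mixed with losses that reflect how acceptable EA is.

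**Working it through.** **1. The plan's own figure.** Sample size gives 36 patients, 18 per arm, with 20% drop-out. No effect size, standard deviation or power is stated, so 36 cannot be derived. Only the drop-out step can be checked: 14 / (1 − 0.20) = 17.5, rounded up to 18; 15 × 1.2 = 18 also fits. This point does not dispute the number; 18 is used below as the size of the EA arm.

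**2. Which patients the listed steps catch.**

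| Patient | Exclusion 5 | Consent (inclusion 6, Design) | Exclusion 3 | Can be randomised? |
|---|---|---|---|---|
| Rejects or fears needles | Caught | Probably caught | Not relevant | No |
| Accepts needles, refuses EA from the outset | Not named | Should be caught | Not relevant | Mostly no |
| Accepts both at consent, changes mind about current after allocation | Not caught | Not caught | Not relevant | Yes |
| Willing, but not suitable for current | Not caught | Not caught | Only if the reason is also a listed severe disease | Yes |

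The last two rows are the gap. Patients in them can be lost because of the current only if allocated to EA, since the other arm receives none.

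**3. What happens to such a patient in the analysis.** Lost before session 1: outside the ITT population, from the EA arm only. Lost after session 1: still inside it, possibly with missing outcomes.

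**4. How often.** The article gives no rate, so assume a share *p* of those randomised (that is, after consent) is affected. Expected number in the EA arm = 18 × *p*. Chance of at least one = 1 − (1 − *p*)^18.

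| Assumed *p* | Expected among 18 | Chance of at least one |
|---|---|---|
| 2% | 0.36 | 1 − 0.98^18 = 30% |
| 5% | 0.9 | 1 − 0.95^18 = 60% |
| 10% | 1.8 | 1 − 0.90^18 = 85% |

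**5. How much it could move the result.** One patient is 1/18 = 5.6% of the arm. If *k* patients are dropped and differ by 1 SD from those who remain (an assumption), the EA mean shifts by *k*/18 SD: 0.056 SD for one, 2/18 = 0.11 SD for two.

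**6. Precision.** For illustration, take a standardised difference of 1, two-sided 0.05 and the normal approximation. Power = Φ(1/√(1/n₁ + 1/n₂) − 1.96). With 18 against 18: Φ(3.00 − 1.96) = 85%. With 16 against 18: Φ(2.91 − 1.96) = 83%. The issue is therefore one-sided selection, not loss of power.

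**The case against.** The strongest reply is that consent already does this work. Patients are told of both arms, have time to consider, and sign before enrollment; a signature is itself an entry criterion. Someone who will not have EA has no reason to sign. The sentence about declining EA follows closely on the consent sentence, so it most naturally describes people who never join. This stands for outright refusal. A reader might infer that patients who reject current are routinely randomised; the documents do not support that. Nor may a refusal rate among otherwise eligible patients be applied to the 18 already randomised, because consent removes most refusers first.

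A reader might also infer that such patients would go untreated, or that EA completers are to be compared with everyone in the acupuncture arm. Neither is established. EA is added to needling, and nothing says that a patient without current would forgo the needles. No completer analysis is planned; only a loss before the first session leaves the analysis set.

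Exclusion 5 might be read to include EA, since exclusion 6 speaks of any type of acupuncture and the Discussion treats EA as a form of it. That reading is possible. But the article uses acupuncture as the name of the comparator arm, and even the broad reading covers rejection or fear, not suitability.

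Finally, the documents name no condition that makes current unsuitable, and the full protocol may contain such a list. That is a fair limit on size. It leaves intact the observation that the published criteria check acceptance of needling and check nothing about the added component. The existence of exclusion 5 alongside the consent criterion also shows that consent alone was not relied on for needling.

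**Conclusion.** The point holds in a limited form. Suitability for electrical stimulation is not confirmed before allocation, and the sentence on declining EA has no stated timing. Losses caused by the current can therefore arise only in the EA arm, and those before the first session drop out of the ITT population on that side alone.

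The effect is probably small. The 30%, 60% and 85% chances rest wholly on assumed rates of 2%, 5% and 10% among those randomised; after consent the lower end is more plausible. The shift of 0.056 SD per lost patient further assumes a 1 SD difference from those who remain. Neither threatens the trial, but in an arm of 18 each such patient counts, and the gap is cheap to close.

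**What to change.** 1. Extend exclusion 5 so that willingness and suitability for both arms, electrical stimulation included, are confirmed for every patient before the envelope is opened. The conditions that count as unsuitable are for the investigators to set; if the full protocol already lists them, refer to that list.
2. State in the Design section that the sentence on subjects who decline EA refers to people who decline before randomisation and are not enrolled.
3. In the Analysis section, keep every randomised patient in the assigned arm, without requiring a first session.

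Cost: one screening item, two wording changes and a few more screen failures.

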### Intervention

Intervention was designed according to record in the ancient book of *Yellow Emperor’s Inner Bible*[28] and according to recent studies of acupuncture as a treatment for CS. Subjects will receive acupuncture at bilateral acupuncture points *Jing-jiaji* (EX-B2.C4), *Jing-jiaji* (EX-B2.C5), and *Jing-jiaji* (EX-B2.C6). Sterile disposable acupuncture needles (40 mm in length and 0.30 mm in diameter; Andy brand, Guizhou Andy Medical Instrument Co., Ltd. (
http://www.andiyx.com; [contact]) will be perpendicularly inserted to a depth of 20 to 30 mm above the *Jing-jiaji* points in both groups. EA protocol was developed in consensus with acupuncturists and experts, who are good at acupuncture. In addition, this protocol is consistent with the STRICTA guidelines for the performance of EA studies
[29].

### Acupuncture group

Acupuncture will be used in the acupuncture group. In this study, acupuncture at bilateral *Jing-jiaji* points for 30 minutes each time, five sessions a week for four weeks will be admininistered.

### Treatment group

In addition to normal acupuncture treatment, EA apparatus (Bio Medical™ Life Systems (
http://www.bmls.com; [contact])) will be connected to the needles for 30 minutes with interrupted waves (0.5Hz, 1 mA), five sessions a week for four weeks.

### Outcome measures

Three well-recognized patient-reported tools will be used to measure the outcomes. NPQ will be used as the primary outcome measure, and MPQ and SF-36 will be used as secondary outcome measures.

### Primary outcome

NPQ will be used to measure the symptoms of CS and function of the cervical vertebrae
[30]. The tool with a higher score reflects a more serious disease state.

### Secondary outcome

The MPQ is a classic tool for assessing the intensity of neck pain, and a higher MPQ score reflects more serious pain
[31]. The SF-36 is a general tool for measuring quality of life
[32]. The tool consists of eight domains that measure quality of life of subjects in physical, mental and social dimensions. A higher score reflects a better quality of life.

## Statistical methods

### Sample size

This study is a pilot study for evaluation of the efficacy of EA on patients with CS and the feasibility of a large clinical trial. Due to the short duration, lasting four weeks, the desired sample size for this pilot study is 36 patients, with 18 for each group, assuming a drop-out rate of 20%, which is the minimum sample size necessary to evaluate the effectiveness of EA
[33].

### Analysis

Data will be analyzed by a statistician blinded to allocation of groups. Statistical analyses will be conducted using SPSS 17.0 statistical software packages ([contact]–3000), and the levels of significance will be reported at *P* < 0.05. The intention-to-treat (ITT) population was defined as the participants who are randomized and received at least one treatment session. The data analysis of baseline characteristics, as well as the primary and secondary outcomes is based on the ITT principle. In addition, analysis of covariance will also be conducted for possible baseline incomparability.

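### The set called intention-to-treat is limited to patients who had at least one session, so it is a modified ITT set, and in this open-label comparison the exclusion can depend on arm

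*Protocol article*

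**What the plan says.** The Analysis section (under Statistical methods) of the protocol article defines the main analysis set: "The intention-to-treat (ITT) population was defined as the participants who are randomized and received at least one treatment session". The next sentence says where it is used: "The data analysis of baseline characteristics, as well as the primary and secondary outcomes is based on the ITT principle". The article names no other analysis population.

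The Design section, below Table 1, puts treatment after randomisation: "After randomization, patients will receive 20-session treatments over a period of four weeks". A patient can therefore be randomised and never treated.

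The Blinding section describes who knows the arm. On the treating staff: "The acupuncturists are in charge of sending randomization information and also receiving notices of the group assignation". It adds that blinding them is not practical. On patients: "it is not possible to prevent subjects from knowing whether they have received EA treatment or acupuncture intervention". For the remaining roles it says "it is feasible to blind outcome assessors and statisticians".

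**The concern.** Analysis by intention to treat keeps every randomised patient in the group assigned, so that the groups compared are the groups that chance created. The article's definition adds a condition, receipt of a session, that is met or not met only after randomisation. Its label and its stated principle therefore disagree with its content. Because the definition is written out, it is not a detail that the article has left to a separate analysis plan. A later plan that copied it would inherit the problem.

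A randomised-and-treated set is easiest to defend when the arm cannot influence whether treatment starts, as under double blinding. That defence is not available here. The acupuncturist must know the assignment to deliver it, and the patient is not blinded. Blinding the assessors and the statistician does not help, because the exclusion would happen before they see any data.

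Three things are at stake:

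- The comparison may no longer be fully randomised.
- The baseline table is built on the same set, so it would also omit the excluded patients and could not show any imbalance that their removal caused.
- The result would be reported as ITT although it is not.

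The article also describes the study as a pilot that informs the feasibility of a larger trial. Patients who accept randomisation but never start are feasibility information, and the definition takes them out of the main set.

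**Working it through.** **Definition.** The defect in the definition needs no arithmetic. The ITT principle means all randomised patients, analysed as assigned. The article's set is all randomised patients minus those with no session. The two coincide only if every randomised patient has at least one session.

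**Inputs for the size.**

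- From the Sample size section: 36 patients, 18 per group, drop-out assumed at 20%. Patients are "allocated randomly into an EA group and an acupuncture group in a 1:1 ratio".
- Assumed, not in the article: the number *k* of untreated patients excluded from one arm, and the difference *d* (in SD units) between the mean outcome of the excluded and the retained patients. I take *d* from 0.5 to 1.0.

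**The plan's own figure.** The article gives no effect size, SD or power, so 18 per group cannot be rebuilt in full. The drop-out step alone fits 14 evaluable patients per group, since 14 / (1 − 0.20) = 17.5, rounded up to 18. It also fits 15 × 1.2 = 18. The 18 is used below only as a denominator.

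**Formula.** If the retained patients have mean *m* and the *k* excluded have mean *m* + *d*, the mean over all 18 is *m* + (*k*/18) × *d*. Leaving the *k* patients out therefore shifts the arm mean by (*k*/18) × *d*.

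| *k* excluded in one arm | Share of the arm | Shift at *d* = 0.5 SD | Shift at *d* = 1.0 SD |
|---|---|---|---|
| 1 | 1/18 = 5.6% | 0.028 SD | 0.056 SD |
| 2 | 2/18 = 11.1% | 0.056 SD | 0.111 SD |
| 3 | 3/18 = 16.7% | 0.083 SD | 0.167 SD |

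The last row is an extreme case. A 20% drop-out over the whole study is 0.20 × 18 = 3.6 patients per arm, so three non-starters would use nearly all of it before the first session. If both arms lose patients, the shift in the contrast is the difference between the two arm shifts. With one exclusion per arm and the same *d*, it is zero.

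**Yardstick.** With 18 per arm, the standard error of the difference is √(2/18) = 0.33 SD. One exclusion at *d* = 1.0 is 0.056 / 0.333, about a sixth of that. Two are 0.111 / 0.333, a third.

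**Power.** For an assumed difference of 1 SD (two-sided 0.05, normal approximation), power is 85.1% at 18 v 18 and 81.6% at 18 v 15. The loss is small even in the extreme case. The issue is possible bias and the wrong label, not power.

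**The case against.** The strongest reply is that very few patients, perhaps none, will be affected. Table 1 puts randomisation and the start of treatment in the same Week 0 column. Patients are told in advance that they may be assigned to either arm, and those who fear or reject acupuncture are excluded. The shifts above are small against a standard error of 0.33 SD, and the study is a pilot. All of this stands. It bears on how serious the flaw is, not on whether the definition is wrong.

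Two stronger readings are tempting, and the article supports neither:

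- A reader might infer that patients who leave on learning their arm are removed from the analysis. The Blinding section speaks only of patients knowing what they have received. Both arms are needled at the same points, and EA adds the connected apparatus. A patient who discovers the arm at the first session and then leaves has had a session, so the definition keeps that patient. Only someone who knew the arm before session 1 could be lost in this way, and the article does not say that patients are told then.
- A reader might infer that the protocol expects refusals of EA after allocation, from the Design sentence "For subjects who decline to agree to participate in EA, other treatment options will be available". That sentence directly follows the text on consent before enrolment. It most naturally means people who decline to join and are never randomised, so it is no support for this point.

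The article offers two partial safeguards. The Quality control section requires drop-outs and withdrawals to be recorded with reasons, during treatment and follow-up. It does not say by arm or before the first session, and recording patients does not return them to the analysis. The planned analysis of covariance adjusts for measured baseline differences among the patients analysed and cannot restore those left out.

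**Conclusion.** The point holds as one of definition and labelling, with a possible but unquantified bias. The set called ITT is a modified ITT set. It does not match the principle that the article invokes, and no all-randomised analysis is named beside it. Exclusion related to arm is possible because acupuncturists know the assignment and patients are not blinded. The article does not show that it will happen.

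The likely size is modest: about 0.03 to 0.06 SD in one arm's mean for one exclusion and 0.06 to 0.11 SD for two, with the direction unknown. These figures rest on the assumed 0.5 to 1.0 SD difference and on all exclusions falling in one arm. A shift of 0.17 SD needs three non-starters in the same arm, all 1 SD different, and nothing in the article supports that. The definition should be corrected, but it does not by itself undermine the trial.

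**What to change.** 1. Define the ITT population as all randomised participants, analysed in the group assigned, whatever treatment they received. Use it for the baseline, primary and secondary analyses.
2. Ask randomised patients who never start treatment to complete the NPQ at the scheduled visits. Treat the outcomes of those who do not agree as missing, and handle them with the same stated method as other missing outcomes.
3. Keep the set with at least one session as a sensitivity analysis, labelled modified ITT.
4. Report the number of randomised patients with no session, by arm and with reasons.

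The cost is low but is more than a change of wording. The Week 0 NPQ gives only a baseline score, so non-starters must be followed to three months after the treatment phase or their outcomes handled as missing. For the few patients likely to be involved, this is a small burden. The article reports recruitment as under way, so the change should be made and dated before any comparison of the arms is seen.
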